### Data collection

Data, as specified earlier, will be collected, by the local researcher, from GP practice and care home paper and/or digital records. Data will be coded and entered into either paper Case Record Forms (CRFs) or electronically using tablets. Data entered on paper records will be subsequently entered into a centrally held Norwich Clinical Trials Unit (NCTU) CHIPPS REDCap [28] database by local researchers. Data collected electronically will be entered into the REDCap database at the time of data collection if there is Internet connectivity, or if working off-line, at the next time the device is synchronised. Data will be protected using established NCTU procedures.

### Data management

Data management is detailed in the Data Management Plan version 1: 21 November.2017. Local research staff will receive training in all aspects of data collection and management. Identification logs, screening logs and enrolment logs will be kept at each of the four University locations in a locked cabinet within a secured room. All data will be handled in accordance with the General Data Protection Regulations 2018. All participants (GPs, care homes and residents) will be given a unique study Participant Identification Number (PIN). Data will be entered under this identification number onto the centrally held database stored on the servers based at NCTU. Access to the database will be controlled with unique usernames and encrypted passwords, and restricted to members of the CHIPPS study team, and external regulators if requested. The servers are protected by firewalls and maintained according to best practice. The physical location of the servers is protected by CCTV and security door access.

The database and associated code lists have been developed by the Study Coordinators in conjunction with NCTU. The database software (REDCap) provides a number of features to help maintain data quality, including: maintaining an audit trail, allowing custom validations on all data, allowing users to raise data-query requests, and search facilities to identify validation failure/missing data.

Once data entry is complete the database will be locked prior to any trial analysis or unblinding. The Data Management Team will provide a read-only link for the Trial Statistician to access the data. After completion of the study the database will be retained on the servers of NCTU for on-going analysis, for 10 years.

The screening and enrolment logs will remain at the care home. For recruitment monitoring purposes, identifiable patient information will be redacted, and pseudoanonymised copies of these logs being taken to the research office. Following consent, identifiable (consented participants only) screening data, linked to the Participant Identification Number, will be held locally at the University research office, in a locked filing cabinet. After completion of the study the identification, screening and enrolment logs will be securely archived at each University research office for 10 years, unless otherwise advised by NCTU.

### Sample size

A sample size of 880 (440 in each arm) would detect a decrease in fall rate from 1.50 per individual over 6 months to 1.178 with 80% statistical power. These assumptions are based upon data from the CAREMED [29] study, which found a fall rate of 1.5 per individual over a 6-month period and an intraclass correlation coefficient (ICC) no greater than 0.07 for the endpoint of interest. The detectable difference (from 1.5 to 1.178) is a relative reduction of 21% which is half that detected within a UK-based, pharmacist-led medication review service provided to care homes [30]. The CAREMED trial indicated a mortality rate of 33% and further loss to follow-up of 5% over 12 months. Thus, a reasonable estimate of total losses due to mortality or other reasons over 6 months would be 20%, and is taken into account in the above. However, we will use data, where possible, up to the point at which someone withdraws from the study.

To recruit 880 resident participants there will be a recruitment target of 44 triads, with a mean of 20 participants from each, a loss rate of no more than 20% and an ≤ ICC of 0.05.

### Statistical methods

An intention-to-treat analysis will be conducted. The primary outcome (‘falls per resident’) will mostly likely follow a Poisson distribution and a between-group comparison to estimate the difference in falls will be made using a Poisson Regression model. This model will include baseline fall rate, prognostic variables (specified prior to analysis) and group as a fixed factor. The unit of analysis will be the individual participant but, due to the study design incorporating ‘clustering’ these unit outcomes are likely to be correlated. Therefore, a Generalised Estimation Equation (GEE) approach will be used. The Poisson assumption will be assessed with ‘fit’ statistics and, if appropriate, a Zero Inflated Poisson, or a Poisson model with an over-dispersion term will be considered. An analogue GEE model will be used for secondary outcomes, with an appropriate change to the error distribution (e.g. Normal). The estimate of the between-group difference will be provided with a 95% confidence interval and tested at the 5% significance level.

There are currently no plans for any subgroup analyses.

### Safety reporting of Serious Adverse Events

The processes for the recording of SUSARs (Sudden Unexpected Serious Adverse Events), SAEs (Serious Adverse Events) and AEs (Adverse Events) and near misses in PIP documentation, GP and care home records, notification to NCTU, CI review, expedited and periodic reporting to REC will be documented in the study-specific Safety Management Plan.

For the purposes of this trial, SAEs are defined as inpatient hospitalisation and death. The expedited, i.e. immediate reporting is required if they are:
*related* to the study (i.e. they resulted from the intervention) and*unexpected* (referred to hereafter as SUSARs)

A mixture of prospective and retrospective SUSAR notification will be used.

Prospective: from the beginning of the intervention until 30 days after the intervention ends GPs will be asked to report SUSARs immediately via a SUSAR Form to a dedicated NCTU safety email address.

Retrospective: a systematic retrospective collection of SAEs will be conducted in both intervention and control practices, whereby the NCTU Trial Manager will contact every participating care home once a month and ask about any SAEs. Deaths and hospitalisations in both arms will also be reported to the REC via the annual report.

The causality assessment of the SAE should be given by the GP. If the GP identifies a positive causality (i.e. the SAE is linked to the PIP intervention and is, therefore, a SUSAR) then this is signed off by the CI. The GP must assess the causality of all SAEs in relation to the PIP intervention using the definitions in the table below. If the event is classified as ‘serious’ and assessed as being related to the PIP intervention then a SUSAR Form must be completed and NCTU notified within 24 h.

All staff involved in the care of study participants (i.e. PIPs, care home staff, any other healthcare professionals) will also be asked to report, immediately, to a separate dedicated email address ([contact]), any events about which they are concerned. NCTU can be notified of any further safety concerns or near misses by all staff involved in the care of study participants via a study-specific safety email address Table 2.

**Table 2 Tab2:** Serious Adverse Event (SAE) causality definitions

Event type	Causality assessment	Description
SAE	Unrelated	There is no evidence or rationale for any causal relationship
SUSAR (Sudden Unexpected Serious Adverse Event)	Likely to be related	There is evidence, and a rationale, to suggest a causal relationship and other possible contributing factors can be ruled out

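### Table 2 gives no causality grade to a serious event whose link to the intervention is plausible but where other causes remain open, and the section gives two different rules for what counts as a SUSAR

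*Protocol article*

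**What the plan says.** All the text at issue is in the Protocol article, section Safety reporting of Serious Adverse Events. SAEs are limited to deaths and inpatient admissions.

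**Grading.** The instruction is mandatory and covers every SAE: "The GP must assess the causality of all SAEs in relation to the PIP intervention using the definitions in the table below". Table 2 then offers two rows:

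- SAE, 'Unrelated': "There is no evidence or rationale for any causal relationship".
- SUSAR, 'Likely to be related': evidence and a rationale must exist "to suggest a causal relationship and other possible contributing factors can be ruled out".

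**Expedited reporting.** The opening rule reads "The expedited, i.e. immediate reporting is required if they are" and lists two conditions. The first is that the event is related "to the study (i.e. they resulted from the intervention) and"; the second is that it is unexpected. Events meeting both are "referred to hereafter as SUSARs". Further down, the sentence on GP causality says "If the GP identifies a positive causality (i.e. the SAE is linked to the PIP intervention and is, therefore, a SUSAR", and the next rule requires a SUSAR Form and notification of the trials unit within 24 hours for any serious event judged related to the intervention. Neither of these later sentences mentions unexpectedness.

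**The concern.** A causality scale that must be applied to every event has to give every event a grade. This one appears to leave out the middle: events where a link is plausible but other explanations cannot be excluded. In this trial that is likely to be a common situation. The Background describes residents as frail, with several illnesses and many regular medicines, and calls falls multifactorial. The intervention moves prescribing responsibility to the pharmacist, so a death or admission after a medication change is the sort of event the safety system should be able to classify. If the GP has no grade for it, whether the 24-hour form is completed depends on how each GP fills the gap, and practice may differ between sites.

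The second problem is that a GP or trials-unit manager reading the section cannot tell whether a related but expected SAE is a SUSAR. One rule says no and the others say yes.

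**Working it through.** No arithmetic is at issue. The check asks two questions of the text: do the grades cover every case, and do the SUSAR rules agree?

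**Check 1: coverage of Table 2.** The two definitions use three conditions: evidence of a causal link (E), a rationale for one (R), and other contributing factors ruled out (X). 'Unrelated' requires neither E nor R. 'Likely to be related' requires E, R and X together.

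| Evidence or rationale for a link | Other factors ruled out? | 'Unrelated' | 'Likely to be related' |
|---|---|---|---|
| Neither | Either way | Yes | No |
| Both | Yes | No | Yes |
| Both | No | No | **No** |
| Only one of the two | No | No | **No** |
| Only one of the two | Yes | No | **No** |

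The last three rows have no grade. The third and fourth are the ones that matter in practice: there is some evidence or rationale, which rules out the lower grade, and other contributors remain open, which rules out the upper grade. The grades are therefore not exhaustive. The table shows only which kinds of event are uncovered, not how often each occurs.

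**Check 2: consistency of the SUSAR rules.** Take an SAE judged related to the intervention, and ask whether expectedness changes its status under each statement.

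| Statement in the section | Related and unexpected | Related but expected |
|---|---|---|
| Opening rule for expedited reporting | SUSAR | **Not a SUSAR** |
| Sentence on positive causality: "the SAE is linked to the PIP intervention and is, therefore, a SUSAR" | SUSAR | SUSAR |
| Rule for the form and 24-hour notice | Form required | Form required |
| Table 2, second row (if other factors are ruled out) | SUSAR | SUSAR |

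The right-hand column conflicts. The article's expansion of the abbreviation contains the word unexpected, and Table 2 repeats it in the row label, but the row's description tests causality only.

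**How the two checks bear on each other.** The relatedness threshold also moves within the section, from having resulted from the intervention, to being linked, to being related, to having other factors ruled out. The ruled-out condition in Table 2 narrows what reaches expedited reporting; dropping unexpectedness widens it. The two defects pull in opposite directions and should be treated separately.

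**The case against.** **The events are captured anyway.** This largely stands. The trials unit asks every participating care home about SAEs once a month, in both arms. Deaths and hospitalisations in both arms go to the ethics committee each year. All staff caring for participants are asked to report at once anything that worries them, with no causality threshold, and there is a route for near misses. Mortality and hospitalisation are secondary outcomes, the DMC examines safety data, and a geriatrician checks a random 20% of care plans. A reader might infer that safety oversight, or the pilot's safety criterion, rests on a count of related events that the table keeps near zero. The article does not support this: nothing in it makes that count the basis of oversight. What these routes do not supply is a grade that decides whether the 24-hour form is due.

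**Doubtful events will be filed as 'Unrelated'.** This is also tempting and also unsupported. By its own wording that grade is closed to a GP who sees any evidence or rationale. The trigger sentence speaks only of an event judged related, so the GP could equally report. The text leaves the outcome undefined; it does not default to non-reporting.

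**The Safety Management Plan holds the detail.** The article does send the recording and reporting processes to that plan, which is not shown. But the article itself fixes the two grades and states the conflicting triggers, and a separate plan cannot make both triggers true.

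**A row of Table 2 may be missing from the copy read.** In that copy the table is broken between its two rows. Both rows are complete and nothing points to a lost one, but the published table should be checked. The conflict over unexpectedness does not depend on this.

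**Dropping unexpectedness only produces more reports.** True of its direction, but a reporting rule that gives two answers for the same event still has to be settled.

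**Conclusion.** Both parts hold on the text. Table 2 is not exhaustive: an SAE with some evidence or rationale for a link, but with other contributors not excluded, has no defined grade and may not trigger the 24-hour SUSAR Form. Separately, the opening rule requires relatedness and unexpectedness, while two later sentences and Table 2 require relatedness alone.

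The consequence is limited to grading and expedited reporting, since other routes would probably still bring such events to light. Its size cannot be put in numbers from the article. A reader might try to size it from the 33% twelve-month mortality in the Sample size section, which on a linear split gives 440 × 0.33 / 2 ≈ 73 deaths per arm over six months. That is background mortality taken from an earlier trial; it does not say how many events would fall between the grades, and control residents do not receive the intervention.

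The conclusion assumes that Table 2 has only the two rows seen. Which reporting rule is the right one is not judged here; the passages must be reconciled.

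**What to change.** 1. Add an intermediate causality grade to Table 2 for events with a plausible rationale where other factors are not excluded, worded so that the grades together cover every SAE.
2. State whether that grade triggers the SUSAR Form and notification of the trials unit.
3. Reconcile the opening rule, the two later sentences and Table 2 to one SUSAR definition that says whether unexpectedness is required, and use it throughout, including in the Safety Management Plan.

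The cost is an amendment to the table and the form, and possibly some more expedited reports, depending on the choices made in steps 2 and 3.

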### Trial management

The trial is overseen by a Trial Management Group (TMG) comprising the Programme Chief Investigator, The Trial Co-Chief Investigators, the local Principal Investigators, the Senior Programme Manager, the NCTU Manager and the Programme Administrator. The trial is advised by a Programme Steering Committee (PSC) which provides expert oversight of the trial, making decisions as to the future continuation (or otherwise) of the trial, by monitoring recruitment rates, approving proposals by the TMG concerning any change to the design of the trial, as well as receiving letters of feedback from the independent Data Monitoring Committee (DMC). The DMC comprises a statistician, an academic pharmacist with an interest in patient safety, and an academic GP (Chair) with extensive trials’ experience. The DMC has a remit to monitor the safety of the trial participants through examination of trial safety and efficacy data, thereby providing advice to the Chair of the Programme Steering Committee (PSC). The DMC Chair informs the Chair of the PSC if, in the view of the DMC, one trial arm is clearly indicated or contraindicated (for all participants or a particular category of participants), and there is a reasonable expectation that this new evidence would materially influence patient management.

There is a study Quality Management and Monitoring Plan (version 2: 1 June.2018) which details the procedures for quality control and data monitoring by the NCTU. The study will also be subject to random monitoring by the host Universities and local Research and Development Departments.

## Discussion

The internal pilot study confirmed the feasibility of all study processes and no safety concerns were identified. The results will be reported in full when the main trial findings are published. Resident recruitment is ongoing and on target. The trial is expected to complete in early 2020. The TMG is grateful for the support of the TSC and DMC who have confirmed that to date there are no concerns.

The study should provide important information on the clinical and cost-effectiveness of involving pharmacists in general practices and care homes –a policy being widely rolled out across all home nations but with no RCT of evidence. The trial is part of a programme of work, part of which has been to develop a training programme for pharmacists involved in care homes and this will be made publicly available. The study also includes a detailed process evaluation and, taken together with the trial results, the findings should allow recommendations to be made about the optimum way to roll out and manage this wider role for pharmacists. At a time when the UK population is ageing, the results will be relevant both to care home residents and frail, community-dwelling older adults (Additional file 4).

## Data Availability

Requests for access to the final trial dataset will be considered, and approved in writing where appropriate, after formal application to the TMG/PSC. Considerations for approving access are documented in the PMG/PSC Terms of Reference.
